#### Experiment 2 Procedure: Waist

First, to assess the degree of baseline body size discrepancy participants will complete the Body Visualizer task. The initial ‘weight’ of the avatar will be set to match the participant’s ± 25%. Participants will be instructed to adjust the avatar's body's 'weight' dimension. Whether the initial weight was + 25% or − 25% will be counterbalanced over two repeats, one after the other, and which together allows calculating the degree of body size discrepancy for each condition, by averaging the two responses. Later, the experimenter will measure the width of the participant’s waist using a paediatric stadiometer. Specifically, the location of the waist will be “the minimum horizontal circumference around the body at waist height” in line with the ‘Standard Terminology Relating to Body Dimensions for Apparel Sizing’ [51].

Subsequently, participants will be first required to complete an "anchor" task. In this task, participants will be asked to press and pull out their waist twenty times, an action that will trigger the ‘anchoring’ tone on each occasion. After completing the anchor task, a practice task will be presented, one trial for each feedback condition.

In each practice trial, participants are required to look straight at the red fixation point in the middle of the table and complete the simple action of pressing and pulling their waist with both hands while keeping them fixed to their waist (see Fig. 2. One of the three experimental tones ('ascending,' 'descending,' or 'constant') is triggered by the pressing and pulling action. Participants are instructed to continue pressing and pulling their hands until the sound is no longer audible and, once the sound stops, to relax both hands (while keeping touching their waist). They will then be asked to determine the width of their waist by having the experimenter adjust the two visible points on the ruler clips. As a paradigmatic example, this adjustment will be done as follows: as in Keizer et al. [18], first, the experimenter will move both clips closer together at a continuous speed until the participant indicates that the clips have reached the perceived waist width position with a "Stop" signal. Similarly, the starting point of the aperture width (A) will be set at A = 2.0 × W (W = waist width in cm). This will be repeated while the clips are closed, and while the experimenter pressed and pulled them apart. The initial position of the clips will be counterbalanced across the trials. For both conditions we will collect waist width estimation measurements. Similarly, for each condition, the feeling of confidence with the estimation will be assessed and an average score will be obtained.

As in the finger experiment, the experimenter will use the measurements on the back of the ruler to record the position of the clips, rounding to the nearest 0.5 cm. After completing the practice task, the experimental block will begin. They will repeat the task for thirty trials. Each experimental tone will be presented ten times. The order of the trials will be randomized among participants. Participants will have an opportunity to rest after each 10 trials.

After the experimental block, participants will be asked to repeat the task for three more trials (one for each sound condition, their order randomized across participants) in order to collect self-report measures (questionnaire block). After each trial, participants will complete a questionnaire that assesses their subjective experience during the task [see the Additional file 3]. In addition, to assess the degree of post-experiment body size discrepancy, participants will complete the Body Visualizer task. They will repeat the task for three trials, one trial for each feedback condition. The order of the trials will be randomized among participants.

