Body visualizer task [44]	To assess the ability to accurately estimate body size (body size discrepancy) as well as the effects of sound feedback on perceived body size. Participants will adjust the weight related dimension of the body of a 3D avatar displayed on the screen to correspond to their perceived body size. Accuracy will be calculated according to the formula (estimated/actual body size) × 100 also-called body perception index (BPI) [45]. Specifically, a negative value represents an underestimation, whereas a positive value represents an overestimation	X		X

Body weight will be measured to the nearest 0.1 kg/% by means of a calibrated digital body fat scale (Sinocare CW 286). The Body feelings questionnaire will be directly built into Google Form and completed on a 10.1″ Android tablet (Lenovo M10)

^†^Spanish Version of the Eating Disorder Examination Questionnaire [46]

^‡^Spanish version of the Highly Sensitive Person Scale [47]

^§^The Multidimensional Assessment of Interoceptive Awareness [48]

Inclusion criteria will be: (a) normal (or corrected) auditory acuity; (b) sex: females (sex assigned at birth); (c) females within the healthy range of BMI (between 18.5 and 24.9) in order to reduce the likelihood of medical comorbidities that could affect the results (according to the World Health Organization index (WHO) [49]). Nevertheless, we recognize that weight/body mass index is not the sole predictor of potential co-occurring medical conditions. By doing so, we also avoid a potential confounding variable reported by [24]. This is in line with the criteria of healthy participants usually used in the field of eating disorders and body illusions research (e.g., [16]). Exclusion criteria: (a) lifetime history or presence of any significant brain injury, neurological condition, auditory pathology; (b) lifetime history or presence of a mental illness measured by self-report measures and screening questions; (c) lifetime history of underweight or overweight; (d) current use of psychotropic drugs (e.g. antidepressants) or intake of recreational synthetic or natural drugs; (e) inability to understand Spanish; (f) inability to provide consent; (g) out of age range; (h) pregnant status.

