**Fig. 2 Fig2:**
[figure not shown]
Schematic depiction of experimental procedure and timeline of events for participants with subthreshold ED symptomatology and control participants. R = Randomized order

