### General experimental procedure

Table 1 shows an overview of study measures and data collection time points and Fig. 3 shows a schematic representation of the experimental procedure. After reading the information sheet and signing the information consent, participants will complete the S-EDE-Q. Participants eligible to take part will be invited to the lab at Loyola Andalucia University. The experimental procedures will be implemented, and all data will be collected, by a postgraduate Ph.D. researcher trained by senior members of the research team. After reading the information sheet and signing the information consent, demographic data (age and BMI) will be collected. Later, participants will complete two questionnaires related to the secondary aim (see Table 2). The Multidimensional Assessment of Interoceptive Awareness Scale (MAIA) (to assess interoceptive body awareness) and the Highly Sensitive Person Scale (HSPS) (to assess sensory-processing sensitivity). The same participants will complete both Experiments 1 and 2.

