The procedure and materials of each of the experimental blocks is described in next sections and in Figs. 1 and 2. In brief, in the experimental block each experimental tone (‘ascending’, ‘descending’, ‘constant’), will be presented ten times. The order in which the tones are presented will be counterbalanced across participants following a within-subject design. After the experimental block is completed, participants will be asked to repeat the task of pulling their right finger (Experiment 1) or waist sides (Experiment 2) while listening to a tone for three more trials, one trial for each feedback condition, with the presentation order randomized across participants. Participants will be asked to complete a body feelings questionnaire after each feedback condition (questionnaire block) [see Additional file 2 and 3 for more details]. Additionally, for Experiment 2, a baseline and post-experiment body size discrepancy measure will be collected. The full experimental procedure will take approximately 120 min with a 5-min rest interval between both experiments. After completing the study, a debriefing session will be carried out.

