### Statistical analyses

#### Primary aim: auditory-driven changes in body perception Baseline measures

To determine differences between the groups, analyses will be performed with a Student's t-test paired comparison (for normal distribution) or Wilcoxon tests (for non-normal distribution) for ED symptomatology (EDE-Q), interoceptive body awareness (MAIA), sensory-processing sensitivity (HSPS) and body size discrepancy (Body visualizer tool).

#### Experiment 1 and Experiment 2

For the estimations of body part position/size, confidence task and items from the body feelings questionnaires we will follow a 2 × 3 ANOVA within-between interaction repeated-measures design (see Table 2). Specifically, we will use non-parametric ANOVAs on aligned rank (ART) data, suitable for ordinal data, using the R package ARTool [56]. The ANOVAs will involve a group factor with 2 levels (subthreshold EDs and controls) and a feedback condition factor with 3 levels (‘ascendent’, ‘constant’, ‘descendent’). Prior the analysis, assumptions of independence, normality and sphericity will be checked. As in [24], we will include the degree of body size discrepancy as covariate in case of significant baseline differences. Appropriate post-hoc tests will be conducted in case of significant differences.

**Table 2 Tab2:** ANOVA 2 × 3 design

Group	Feedback condition		
	Ascendent	Constant	Descendent
Subthreshold EDs	Subthreshold EDs–Ascendent	Subthreshold EDs–Constant	Subthreshold EDs–Descendent
Controls	Controls–Ascendent	Controls–Constant	Controls–Descendent

For body size discrepancy, we will follow a 2 × 3 ANOVA within-between interaction repeated-measures design (see Table 3). The ANOVAs will involve a group factor with 2 levels (subthreshold EDs and controls), a time factor with two levels (baseline and post-experiment) and a feedback condition factor with 3 levels (‘ascendent’, ‘constant’, ‘descendent’).

**Table 3 Tab3:** ANOVA 2 × 2 × 3 design

Group	Baseline	Experiment		
		Feedback condition		
		Ascendent	Constant	Descendent
Subthreshold EDs	Subthreshold EDs Baseline	Subthreshold EDs Post-experiment Ascendent	Subthreshold EDs Post-experiment Constant	Subthreshold EDs Post-experiment Descendent
Controls	Controls Baseline	Controls Post-experiment Ascendent	Controls Post-experiment Constant	Controls Post-experiment Descendent

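### The baseline Body Visualizer reading is placed at the start of Experiment 2, so for anyone who does the finger experiment first it is neither a pre-exposure value nor a pre-outcome covariate for Experiment 1

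*Protocol article*

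**What the plan says.** The section Experiment 2 Procedure: Waist starts with the avatar task: "First, to assess the degree of baseline body size discrepancy participants will complete the Body Visualizer task". It consists of two adjustments, one starting 25% above and one 25% below the participant's own weight, and the two are averaged. The General experimental procedure also assigns the reading to that experiment: "for Experiment 2, a baseline and post-experiment body size discrepancy measure will be collected". The same section lists what happens in the laboratory before the experiments (consent, demographics with BMI, MAIA, HSPS) and does not mention the avatar task. The Experiment 1 procedure does not contain it either.

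Table 1 describes the task ("To assess the ability to accurately estimate body size (body size discrepancy) as well as the effects of sound feedback on perceived body size") and ticks it under Baseline, alongside the questionnaires, and under Experiment 2, with Experiment 1 left blank.

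On sequence, the General experimental procedure says "The same participants will complete both Experiments 1 and 2", in about 120 minutes with a "5-min rest interval between both experiments". The caption of Fig. 2 carries the key "R = Randomized order", but the figure is not shown, so what is randomised there cannot be seen.

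Under Statistical analyses the reading has three uses. Body size discrepancy is compared between the groups among the baseline measures. Under the joint heading for Experiments 1 and 2, "we will include the degree of body size discrepancy as covariate in case of significant baseline differences". In Table 3 it is the baseline level of the time factor.

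**The concern.** Two of the three uses require a value recorded before any experimental sound: the baseline group comparison, and the covariate for the finger outcomes. A reading taken at the start of Experiment 2 meets that requirement only for participants who have not yet done Experiment 1.

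For the others, a group difference in the reading could reflect a different response to the finger tones as well as a pre-existing difference in body size perception. The protocol's own H2 and H3 expect the groups to respond differently to the tones. Such a difference could be reported as pre-existing distortion. It could also trigger the covariate rule, after which the finger outcomes would be adjusted for something measured after them. If the order of experiments varies, the reading has a different meaning for different participants within the same analysis.

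**Working it through.** The documents state no figure for this point (no sample size calculation was made), so the check is one of sequence, followed by an illustration.

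**1. Where the reading falls.**

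| Source | Placement |
|---|---|
| Experiment 2 Procedure: Waist | first step of Experiment 2 |
| General experimental procedure | part of Experiment 2; not listed among the pre-experiment steps |
| Experiment 1 procedure | absent |
| Table 1 | Baseline and Experiment 2; blank for Experiment 1 |

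The Table 1 tick either means the start of Experiment 2, in which case it agrees with the text, or a separate earlier stage, in which case it contradicts the text. It cannot be both.

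**2. What precedes it if Experiment 1 comes first.** From the auditory-trials row of Table 1:
- all tone-triggering actions: 20 anchor + 3 practice + 30 experimental + 3 questionnaire = 56;
- experimental tones: 3 + 30 + 3 = 36, that is 36 / 3 = 12 per condition;
- pitch-changing tones (ascending and descending): 2 × 12 = 24.

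All finger estimates, confidence ratings and finger questionnaires are also complete by then.

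**3. Who is affected.** All 100 participants if Experiment 1 always comes first, about 50 if the order is randomised, and none if Experiment 2 always comes first.

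**4. Use by use, for a participant who does Experiment 1 first.**
- Baseline group comparison: the value is post-exposure. It is biased only if the finger tones shift the reading by a different amount in the two groups.
- Covariate for Experiment 1: the value is recorded after the outcome. This follows from the sequence alone, whatever the size of any carry-over. How far the adjusted result would move cannot be computed from the documents.
- Baseline level in Table 3: the value immediately precedes the waist tones, which is what that contrast needs. No fault here.

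**5. Illustration for the group comparison.** The carry-over is an assumption, because the documents give none. Let δ be the difference between the groups in the shift caused by Experiment 1, in SD units, and s the share of participants who do Experiment 1 first. Assume no true group difference, two independent groups of 50, two-sided alpha 0.05 and a normal approximation. Then

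SE = √(2/50) = 0.2, and P(reject) = Φ(sδ/0.2 − 1.96) + Φ(−sδ/0.2 − 1.96).

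Example: s = 1 and δ = 0.2 give Φ(−0.96) + Φ(−2.96) = 17.0%.

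| δ (SD) | all do Experiment 1 first (s = 1) | half do (s = 0.5) |
|---|---|---|
| 0 | 5.0% | 5.0% |
| 0.1 | 7.9% | 5.7% |
| 0.2 | 17.0% | 7.9% |
| 0.3 | 32.3% | 11.7% |
| 0.4 | 51.6% | 17.0% |

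The same rates describe how often the covariate rule would be triggered with no pre-existing group difference.

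**The case against.** The case on the other side has six parts.

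- **The order is not visible.** It may stand in a figure that is missing from the text at hand, and a missing figure is no fault of the plan. This stands: the point is conditional, and the share affected may be all, about half or none.
- **Table 1 may be the schedule.** The General experimental procedure points to it for the time points, so the waist section may simply describe the task where it is most relevant. This reading is possible. But both procedure passages place the reading in Experiment 2, so the text needs reconciling either way.
- **The link to H1 is inferred.** The analysis section does not name H1, and H1 names no instrument. This is correct. The avatar task is the natural test because Table 1 describes it as the measure of accuracy in estimating body size.
- **Carry-over is speculative.** A reader might infer that the baseline is shown to be contaminated and the test of H1 invalid. The documents do not support that. The tones are balanced over conditions, only 24 of the 56 actions produce a changing pitch, the finger was chosen as a body part without emotional weight, and the avatar task concerns whole-body weight. The one persistence figure in the Background, at least 2 h 45 min, concerns a different illusion in people with anorexia nervosa.
- **Moving the only reading would have a cost.** A reader might infer that shifting it earlier costs nothing. For anyone who does Experiment 1 first, it would put the whole finger experiment between the baseline and post levels of Table 3. This stands and shapes the fix.
- **The study is declared exploratory and the covariate is conditional.** This lowers the severity. It does not turn a post-exposure reading into a baseline.

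**Conclusion.** The point holds in conditional form, with moderate severity. The placement of the baseline avatar reading differs between Table 1 and the two procedure sections, unless the Baseline tick means the start of Experiment 2. Under the procedure text, every participant who does Experiment 1 first gives the reading after 56 tone-triggering actions and after all finger outcomes. For those participants it is not a pre-exposure value for the baseline group comparison, and it is a post-outcome covariate for Experiment 1.

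The two consequences rest on different assumptions. Bias in the group comparison needs carry-over that differs between the groups. Its size is unknown; the assumed shifts of 0 to 0.4 SD give false-positive rates from 5% to 51.6% if all do Experiment 1 first, and from 5% to 17.0% if half do. The covariate's place after the outcome needs only that Experiment 1 came first. The reading remains sound as the pre-waist level in Table 3.

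**What to change.** 1. State the order of the two experiments in the text, and make Table 1, the General experimental procedure and the waist procedure agree on when the avatar task is done.
2. Take the two adjustments (25% above and 25% below) before the first anchor task of whichever experiment comes first. Use only this value for the baseline group comparison and H1, and for any covariate in Experiment 1.
3. Keep the reading immediately before the waist tones as the baseline level of the Table 3 time factor. For participants who do Experiment 2 first, the two readings are the same one.
4. State that Experiment 1 is never adjusted for a reading taken after it.

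The cost is one short repeat of the task, two adjustments, for participants who do Experiment 1 first, plus a few sentences in the procedure and analysis sections. If Experiment 2 always comes first, no extra reading is needed and stating the order and aligning the text is enough. The change has to precede data collection, because a pre-exposure reading that was not taken cannot be recovered.

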## Data analysis plan

IBM SPSS Statistics version 28.0 will be used for data inspection, descriptive and inferential statistics. All the analysis will be done by one of the investigators and it will be cross-checked by a second investigator. For transparency purposes, processed data derived from this study will be available in our OSF project.

### Data inspection

To ensure methodological rigour, prior to running the main analyses, data will be screened for normality through Shapiro–Wilk tests, QQ plots, histograms and values of skewness and kurtosis. We will examine the generated dataset to ascertain any outliers, aberrant response patterns (e.g., deviate from the typical responses) and patterns of missing data. For data related to questionnaires, we plan to use Full Information Maximum Likelihood [52]. For data related to body position/size, we plan to use average imputation as in [25].

### Data management

#### Estimation of body position/size and confidence task

For both experiments, data from the 10 repetitions for each condition will be averaged. As a rule of thumb, for participants with one trial per condition excluded, data for that trial will be replaced by the mean value of the other nine trials for that condition (as in [25]). Conversely, participants with more than one trial per condition excluded, will be excluded from all analyses. Overall, data from trials exceeding three standard deviations from the mean group value will be excluded.

For Experiment 1, we will collect measures for estimated knuckle position and fingertip position, as well as level of confidence with each estimation. In addition, for each trial, the estimated knuckle position will be subtracted from the estimated fingertip position in order to calculate the estimated finger length (as in [25]). For Experiment 2, we will collect waist width estimations, as well as level of confidence with each estimation. For each trial, we will estimate the perceived waist width by averaging the two responses given by the participant (i.e., for the opening and closing aperture).

For each participant a total of 12 summary scores will be calculated [(knuckle position + fingertip position + finger length + waist width limits) × (3 feedback conditions: ‘ascendent’, ‘constant’, ‘descendent’)]. Similarly, a total of 12 summary scores for the confidence task will be calculated [(confidence knuckle position + confidence fingertip position + confidence finger length + confidence perceived waist width limits) × (3 feedback conditions: ‘ascendent’, ‘constant’, ‘descendent’)].

Data from Presentation® software (Version 18.0, Neurobehavioral Systems, Inc., Berkeley, CA, www.neurobs.com) will be recorded into a file in UTF-8 format. The file will be organized and imported into Microsoft Excel 2021 and subsequently into IBM SPSS Statistics version 28.0. Data generated associated with the anchor tasks and practice tasks will be disregarded.

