## Aim and hypothesis

### Primary exploratory aim: auditory-driven changes in body perception

The primary aim of this study is to gain an exploratory understanding of the influence on body perception of non-naturalistic auditory information in participants with subthreshold EDs symptomatology using two body illusions. The scarce literature on the topic precludes us from considering a confirmatory model. As a result, the following hypotheses are all descriptive–exploratory.

**Hypotheses 1 (H1)**: Participants with subthreshold ED symptomatology will differ from participants without ED symptomatology in their degree of body image distortion. This hypothesis is exploratory, as alternatively, both groups may show the same degree of distortion.

H1 is based on previous literature that has shown a conflicting set of results. While there is strong evidence to suggest that young females with ED symptomatology and individuals with EDs tend to overestimate their body size compared to control individuals, some evidence suggests that body image distortions are not specific to this population, implying that they can underestimate their body size [24] or even be as accurate as individuals without ED symptomatology [32].

**Hypotheses 2 (H2)**: Participants with subthreshold ED symptomatology will show stronger auditory-driven body illusions, compared to control individuals.

H2 is based on the traditional hypothesis in support of a stronger influence of external sensory signals, leading to stronger body illusions in people with and subthreshold EDs [15–17].

**Hypotheses 3 (H3)**: Participants with subthreshold ED symptomatology, as compared to without ED symptomatology, will present unusual patterns of results in the finger elongation or shrinking waist illusion, suggesting impairments in the integration of artificial auditory signals into their body image.

H3 hypothesizes that participants with subthreshold ED symptomatology, as compared to people without ED symptomatology, will present unusual patterns of results, that is, the perceived finger elongation or shrinking waist will not necessarily occur in the ascending pitch condition (or not only in that condition, as in [24]. The results will shed light on whether the alteration in the mechanisms integrating auditory signals into body image is present only to natural signals related to body weight/size (e.g., footsteps) or it is linked to any auditory signals.

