The experimenter will use the measurements on the back of the ruler to record the fingertip and knuckle positions, rounding to the nearest 0.5 cm. After each trial, the clips are relocated. After completing the practice task, the experimental block will begin. Participants will repeat the task for thirty trials. Each experimental tone will be presented ten times. The order of trials will be randomized across participants. Participants will be given the opportunity to rest after each 10 trials.

After the experimental block, participants will be asked to repeat the task for three more trials (one for each sound condition, their order randomized across participants), in order to collect self-report measures (questionnaire block). After each trial, participants will complete a questionnaire that assesses their subjective experience during the task [see Additional file 2].

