### Sample size considerations

As these analyses are intended to generate future confirmatory hypotheses, no sample size calculation was conducted. As Jones et al. [53] noted, sample size calculation may be of little value in early exploratory studies where there is a lack of previous research. In an exploratory study, the primary focus is on generating new research questions, identifying patterns and trends, and identifying potential areas for further research, rather than on testing a specific confirmatory hypothesis. As such, the sample size in an exploratory study may not be determined based on statistical power or precision and could be relatively small. Instead, the sample size may be based on the need to obtain a sufficient amount of data to allow for the exploration and identification of meaningful patterns and trends.

In this regard, a total of 100 participants (50 participants in each group) will allow us to gain an exploratory understanding between body perception and non-naturalistic auditory information in participants with subthreshold ED symptomatology. This sample size is the minimum recommended by Brysbaert [54] to seek differences between groups and is also between 30 and 150 participants, that is the sample size usually recommended in exploratory study designs with non-probability sampling [55]. To this end, and based on norms for the Spanish version of the Eating Disorders Examination Questionnaire (S-EDE-Q), we will screen approximately at least 450 young adult females [39].

Due to the limited sample size, we acknowledge that the statistical power for each of the hypotheses proposed in this study to detect differences between groups might not be sufficient according to the traditional standards in experimental psychology (effect size = 0.4, power = 0.80 and alpha value = 0.05) [54]. Therefore, the results should be taken with caution and should be contextualized within an exploratory framework. In case of meaningful results, the present exploratory study will provide the necessary foundation for a formal sample size calculation for a future confirmatory larger-scale study.

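### Outlier trials are judged against the group mean of raw estimates, and two in one condition remove a participant from everything, so the rule can discard consistently extreme people rather than faulty trials

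*Protocol article*

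**What the plan says.** All references are to the protocol article. The cleaning rule is in Data management, under Estimation of body position/size and confidence task. It has three parts:

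- **Trial level:** "data from trials exceeding three standard deviations from the mean group value will be excluded".
- **One excluded trial in a condition:** "data for that trial will be replaced by the mean value of the other nine trials for that condition". Only this part is credited to the earlier finger study, reference [25].
- **Two or more in a condition:** "participants with more than one trial per condition excluded, will be excluded from all analyses".

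The quantities screened are in raw centimetres. For the finger, "the estimated knuckle position will be subtracted from the estimated fingertip position in order to calculate the estimated finger length"; for the waist, "we will estimate the perceived waist width by averaging the two responses given by the participant". Finger length and waist width are measured before each experiment, but neither is used to scale these scores. In each experiment, "Each experimental tone will be presented ten times", and the target is 50 participants per group (Sample size considerations).

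Data inspection adds a general look for outliers and aberrant response patterns, without a within-participant criterion. H1 is that participants with subthreshold symptoms "will differ from participants without ED symptomatology in their degree of body image distortion".

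**The concern.** The spread of raw trials around a group mean has two sources: stable differences between people (body size, habitual over- or underestimation) and trial-to-trial noise within a person. An outlier rule for trials should look at the second. This one looks at the sum.

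Two things follow when the between-person part is large. A woman who consistently reports a very wide or very narrow waist repeats that value over ten trials and easily collects two flags in a condition, although nothing is wrong with her data. A real lapse by an average participant stays inside the wide group band and is kept.

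Because removal is from all analyses, extreme waist estimates would also cost that participant's finger data, questionnaires, Body Visualizer, MAIA and HSPS scores. The selection acts on the level of estimated size, which is close to what H1 compares.

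**Working it through.** The plan gives no expected number of exclusions and no SDs, so there is no figure to reproduce.

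**Inputs from the article:** 3-SD limit around the group mean; removal at 2 or more of 10 trials in any of 3 conditions; 50 per group. **Assumption:** the between-person share of trial variance (ICC). The documents give none, so it is varied. Total variance is set to 1, so the between-person SD is √ICC and the within-person SD is √(1 − ICC).

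**1. How far off must an average participant's trial be?** 3/√(1 − ICC) of her own SDs. At ICC 0.8: 3/0.447 = 6.7.

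**2. How often is a 5-own-SD lapse by a randomly drawn participant flagged?** Φ((5√(1 − ICC) − 3)/√ICC), the other tail being negligible. At ICC 0.8: Φ((2.236 − 3)/0.894) = 0.20.

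**3. How often is a consistent participant with no faulty trial removed?** For someone k between-person SDs from the group mean:
- chance that one trial is flagged: p = 1 − Φ((3 − k√ICC)/√(1 − ICC))
- chance of two or more in a condition: q = 1 − (1 − p)^10 − 10p(1 − p)^9
- chance of removal over three conditions: 1 − (1 − q)^3

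At ICC 0.8 and k = 3: p = 1 − Φ(0.317/0.447) = 0.239, q = 0.731, removal = 0.98.

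| ICC | Own SDs needed (step 1) | 5-SD lapse flagged (step 2) | Removed, k = 2.5 | Removed, k = 3 |
|---|---|---|---|---|
| 0.3 | 3.6 | 98% | not computed | not computed |
| 0.5 | 4.2 | 78% | 0.17 | 0.64 |
| 0.7 | 5.5 | 38% | 0.23 | 0.93 |
| 0.8 | 6.7 | 20% | 0.19 | 0.98 |
| 0.9 | 9.5 | 7% | 0.06 | 0.998 |

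**4. How many are removed, and who?** Simulation of one group of 50, one outcome, 3 × 10 trials, with normal, t (5 df) or lognormal person effects. Mean number removed per 50:

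| ICC | Normal | t (5 df) | Lognormal |
|---|---|---|---|
| 0.3 | 0.2 | 0.4 | 0.6 |
| 0.5 | 0.3 | 0.8 | 0.9 |
| 0.7 | 0.4 | 1.0 | 1.1 |
| 0.8 | 0.4 | 0.9 | 1.1 |
| 0.9 | 0.3 | 0.8 | 1.1 |

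With ICC 0 and normal effects, 7% of those removed are among the two most extreme of the 50, so removal is close to random. With ICC 0.5 to 0.9 the share is 87% to 100%, and 98% to 100% are among the five most extreme. When a removal occurs, the SD of participant means falls by about 8% to 9% (normal) or 14% to 18% (heavy-tailed or skewed).

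**5. A within-person rule for comparison.** Flagging trials more than 3 pooled within-person SDs from the participant's own condition median removes 0.07 to 0.09 per 50 per outcome for ICC 0.3 to 0.9, and flags a 5-SD lapse about 100% of the time.

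**6. Does a group difference shrink?** Two cases at ICC 0.8, with the participant's own group as reference:
- *Whole subthreshold group shifted by 0.4 SD:* 0.398 before exclusion and 0.398 after (0.397 and 0.396 at ICC 0.5). No attenuation.
- *3 of 50 in that group overestimate by 3 or 4 SD:* the true difference is 0.06 × 3 = 0.18 or 0.06 × 4 = 0.24 SD. About 40% or 64% of these participants are removed, and the difference falls to 0.09 or 0.07 SD.

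**The case against.** A reader might infer that the rule biases the group comparison toward zero. The documents do not support that as a general statement. Attenuation needs extreme estimators concentrated in one group, as in the second case of step 6, and no such subgroup is described. H1 is non-directional, and the text under it allows over-, under- or accurate estimation. A uniform shift is untouched.

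A reader might also infer a sizeable loss. Treating the four measures as independent gives 1.5 of 50 at ICC 0.8 with normal person effects and 3.6 with t (5 df) effects. But finger length is computed from the other two finger measures, so these totals overstate the loss; the per-outcome figures are the safer statement. The BMI range of 18.5 to 24.9 and the exclusion of past under- or overweight also narrow raw body size.

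Nor do the documents show that truly aberrant trials are generally missed. At ICC 0.3, 98% of 5-SD lapses are caught, and the actual ICC is unknown.

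H2 and H3 concern illusion strength and pattern, which are contrasts between tones within a person. Selection on overall level touches them mainly through lost participants. The planned aligned-rank ANOVA also limits the weight of extreme people. In the 3-SD subgroup case, the probability that a subthreshold participant exceeds a control moves only from 0.532 to 0.520, although this is a proxy and not the planned test. The same robustness means there is little need to remove such people.

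What stands is the selection itself. The general inspection under Data inspection does not undo it, and neither does the exploratory aim.

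**Conclusion.** The concern holds in a limited form. As written, the rule selects people who are consistently extreme in raw centimetres whenever a substantial part of the trial variance is between people. The extremity may be perceptual or simply a large or small finger or waist. The numbers are modest, from well under one to about one participant per group per outcome, but each removal deletes valid data on every other measure.

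The effect on H1 is possible, not established: it depends on extreme estimators clustering in one group. The ICC and the shape of the person effects are assumptions throughout. The article does not say whether the group mean is that of the study group or the whole sample, or whether it is taken per condition; the mechanism is the same under each reading. This should be changed before data cleaning, but it does not undermine the design.

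**What to change.** Reword the cleaning rule along these lines:

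1. Flag a trial by its distance from that participant's own mean or median in that condition, for example more than 3 pooled within-person SDs.
2. Average the remaining valid trials. This extends what the plan already does for one excluded trial: filling the tenth value with the mean m of the other nine gives (9m + m)/10 = m, the mean of the nine.
3. Drop a participant only from the affected measure, and only if fewer than a stated number of valid trials remain, for example 7 of 10. At that limit the within-person error of the mean rises by √(10/7) = 1.20.
4. Report the currently written rule as a sensitivity analysis, with the number removed per group.

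The cost is a change of data-cleaning wording and one extra analysis; data collection is unaffected. The small downside is that the main analysis departs from the published cleaning rule. The article credits only the single-trial replacement to [25], and point 2 preserves its result.
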